## Abstract

**Background:**

The inspiration of pressure-controlled ventilation is characterized by an initial sharp increase of flow rate. The resulting peak flow rate could induce a disproportionately high mechanical load, transferred from the ventilator to the pulmonary structures. A higher inspiratory ramp time could decrease the peak inspiratory flow rate, which might reduce the mechanical power transmitted to the lungs. This study compares pressure-controlled ventilation with volume guarantee with low and high inspiratory ramp time and the effects on the mechanical load transferred from the ventilator to the patient’s lungs.

**Methods:**

This is a randomized, controlled single-center trial, in which patients receive pressure-controlled ventilation with volume guarantee with short (clinical standard) or increased inspiratory ramp time. Mechanical power will be compared between the two types of ventilation. Further, the effects of the respective ventilation setting will be evaluated with the Horowitz index, the mean airway pressure, and changes in respiratory system compliance. The occurrence of atelectasis will be investigated utilizing electrical impedance tomography. Additionally, lung-specific proteins in patients’ blood will be measured, seeking indications of mechanical stress in their dynamics and postoperative pulmonary complications will be recorded and compared between groups.

**Discussion:**

This trial aims to evaluate the feasibility of decreasing inspiratory flow rate during pressure-controlled ventilation with volume guarantee by increasing inspiratory ramp time and to analyze its effects on mechanical power, oxygenation, respiratory system mechanics, atelectasis, and postoperative pulmonary complications. Furthermore, lung-specific proteins in patients’ blood will be examined in regard to find a novel, helpful biomarker, representing the mechanical load of the lungs. The results of this study could provide valuable information to improve perioperative mechanical ventilation with a reduced mechanical power through a simple an ubiquitously available modification of the breathing pattern, namely increasing inspiratory ramp time. Additionally, identification of a lung-specific biomarker reflecting mechanical load of the lungs might enhance research of lung-protective ventilation.

**Trial registration:**

German Clinical Trials Register (DRKS), DRKS00035496. Registered on 12 November 2024; URL: https://drks.de/search/en/trial/DRKS00035496/details.

Local Trials Register: Freiburger Register of Clinical Studies (FRKS), FRKS005304.

## Introduction

### Background and rationale {6a}

The concept of lung-protective ventilation has been the subject of research for many years. Since the establishment of positive end-expiratory pressure, and the concepts of low tidal volume, respectively low peak inspiratory pressure (driving pressure), current concepts of lung-protective ventilation focus on mechanical power and its reduction [1]. As part of this approach, respiratory gas flow is mentioned in many studies as another possible parameter that could influence ventilator-induced lung injury [1–8]. Reduction of the gas flow could decrease wall shear stress in the conducting airways which mainly depends on airflow velocity and smoother alveolar stretching through a decelerated time profile of the breathing pattern.

In own unpublished preliminary physical simulations with computational fluid mechanics, a reduction of peak inspiratory flow from 60 l∙ml^−1^ to 40 l∙ml^−1^ reduced the velocity of air by 32% with a consecutive 46% reduction of wall shear stress. In a cell model, smoother elongation of bronchus epithelial cells has been associated with reduced production of inflammatory cytokines and oxidative stress [9]. Moreover, limitation of the expiratory gas flow reduced lung damage in animal models [10–13]. Regarding the inspiration, there is only an animal study suggesting that a lower peak inspiratory flow could reduce lung damage [14]. However, the extent to which these results can be transferred to humans is unclear.

During pressure-controlled ventilation with volume guarantee, a lower inspiratory flow rate can be easily achieved by increasing the inspiratory ramp time. In an unpublished preliminary investigation in a physical model of the respiratory system, receiving pressure-controlled ventilation with volume guarantee, a higher inspiratory ramp time resulted in reduced mechanical power compared to a lower inspiratory ramp time.

Therefore, we designed this study to compare perioperative pressure-controlled ventilation with volume guarantee with high to low inspiratory ramp time. We hypothesized that patients ventilated with an increased inspiratory ramp time would be loaded with less mechanical power. To assess the potential relationship between the physical variable and biological effects and with the intention to identify a biomarker, which may indicate the mechanical load of the lungs, we evaluate lung-specific proteins and their kinetics during mechanical ventilation.

### Objectives {7}

The primary aim of this study is to compare mechanical power of patients ventilated with pressure-controlled ventilation with volume guarantee with an increased vs. clinical standard short inspiratory ramp time. Secondary objectives are the evaluation of ventilation efficiency between the two groups in terms of oxygenation, respiratory system mechanics, emergence of atelectasis, and postoperative pulmonary complications. Furthermore, we evaluate the kinetics of lung-specific proteins in patients’ blood in the course of mechanical ventilation.

### Trial design {8}

The study design is reported in accordance with the SPIRIT 2013 Checklist. This is an exploratory pilot study that is monocentric, prospective, randomized, and controlled with blinded patients, unblinded data collectors and blinded evaluators. The study is conducted at the Department of Anesthesiology and Critical Care, Medical Center – University of Freiburg and has been approved by the local Ethics Committee of the University of Freiburg (24-1273_S1/24-1273_1-S1). The trial complies with the principles of the Declaration of Helsinki and the principles of Good Clinical Practice.

## Methods: participants, interventions, and outcomes

### Study setting {9}

The study will be conducted at the Department of Anesthesiology and Critical Care at the Medical Center - University of Freiburg and the Department of Neurosurgery at the Medical Center - University of Freiburg. All patients will undergo neurosurgical procedures to ensure a longer time of mechanical ventilation with minor tissue damage.

## Eligibility criteria {10}

Inclusion criteria:Patients scheduled for elective brain surgery with an expected duration of at least 4 h in supine positionPatients must be able to give informed consent

Exclusion criteria:Patients under the age of 18Patients are unable to give consentBody mass index greater than 35 kg/m^2^American Society of Anesthesiologists physical status classification >3Patients with a pacemaker, implantable cardioverter-defibrillator, or cardiac resynchronization therapyPregnancyAnemiaPatients with terminal pulmonary diseaseLong-term use of immunosuppressants

Drop-out criteria:Transfusion of blood products

### Who will take informed consent? {26a}

The principal investigator will obtain written informed consent from potential participants. After patient screening, potential participants will receive information about the study on the day before their surgery. This information will include both spoken and written details about the study, its procedures, and any risks. Patients can refuse their consent at any time without explanation.

### Additional consent provisions for collection and use of participant data and biological specimens {26b}

There are no additional consent provisions for collection and use of participant data and biological specimens in ancillary studies.

## Interventions

### Explanation for the choice of comparators {6b}

The aim of this study is to investigate the mechanical load transferred to patient’s lungs in dependence of the inspiratory ramp time during pressure-controlled ventilation with volume guarantee. Mechanical power is the most recent variable for assessing the delivered mechanical energy to the patient’s respiratory system [1]. Furthermore, the mechanical power is sensitive enough to discriminate between fine adjustments of mechanical ventilation to assess their potential contribution to improved lung-protective ventilation. Additionally, mechanical power can be determined reliably and continuously over a longer period of ventilation without additional risks for the patients.

## Intervention description {11a}

### Ventilation protocol

In this study, patients will receive a pressure-controlled ventilation with volume guarantee with a tidal volume of 8 ml∙kg^−1^ of predicted body weight, with an inspiratory oxygen fraction between 0.3 and 0.5. The breathing rate will be adjusted to maintain end-expiratory carbon dioxide partial pressure in the range of 32 to 45 mmHg. Positive end-expiratory pressure will be set at 7 cmH_2_O for all patients. Patients of the intervention group will be ventilated with the longest available inspiratory ramp time permitted by the ventilator and with an inspiratory-to-expiratory time ratio of 1:1 to 1:1.2 to facilitate the longest possible inspiratory ramp time. Patients of the control group will be ventilated with a short inspiratory ramp time (0 s) with an inspiratory-to-expiratory time ratio of 1:1.9 to 1:2.1.

### Anesthesia

Besides ventilation settings, both patient groups will receive the same standardized anesthetic management. After establishing standard monitoring (non-invasive blood pressure measurement, pulse oximetry, electrocardiogram), and additional placement of an electrode belt for electrical impedance tomography (EIT), patients will be preoxygenated with a tight-fitting face mask to achieve an end expiratory oxygen fraction > 0.8. Subsequently, anesthesia induction with a bolus of Sufentanil (20–50 µg) and a target-controlled infusion of propofol (5.0 to 7.0 μg·ml^−1^ effect site concentration, Schnider model) will be started, followed by relaxation with rocuronium (0.6 mg·kg^−1^ body weight). Depth of anesthesia will be measured with the BIS VISTA Monitoring System (Covidien, Dublin, Ireland). Three minutes after administration of the relaxant, endotracheal intubation will be performed. Afterwards, ventilation according to the protocol will be started until the end of the surgical procedure. An arterial line will be established for continuous blood pressure measurement and arterial blood gas analysis. Perioperative anesthesia will be maintained with a target-controlled infusion of propofol and a continuous infusion of remifentanil 0.2–0.4 μg∙kg^−1^∙min^−1^ aiming for a bispectral index between 20 and 50. A combination with inhalation of 0.3–0.5 MAC sevoflurane may be used if required. Fluid management will be performed in standardized fashion according to the institutional protocol.

### Criteria for discontinuing or modifying allocated interventions {11b}

The attending anesthesiologist can intervene during the complete period of ventilation, if, in his opinion, the modification of ventilation poses a risk to the patient. The anesthesiologist may modify or discontinue the assigned mode of ventilation. At this point, further recording of ventilation data will be stopped and only data up to this point will be included in the evaluation. Furthermore, in case of an increased blood loss, requiring blood transfusion, collecting blood for the study will stop and the patient will be excluded from further participation in the study.

### Strategies to improve adherence to interventions {11c}

The study director will oversee data collection and conduct regular checks to ensure adherence to intervention protocols. If there are any mistakes in recorded data, this will be reported to the study director, who will take further action.

### Relevant concomitant care permitted or prohibited during the trial {11d}

Both study groups receive comparable concomitant care and will be treated equally.

### Provisions for post-trial care {30}

After the surgical intervention, the patients will be transferred either to the post anesthesia care unit and then to the regular ward or to the intensive care unit, based on their specific circumstances. All patients will be monitored by the study team for 7 days after surgery to detect any postoperative pulmonary complications or other adverse events. If postinterventional complications occur, they will be reported to the study director, who will take further action.

### Outcomes {12}

The study compares two strategies of ventilation, focusing on the effects of a long compared to a short inspiratory ramp time during pressure-controlled ventilation with volume guarantee.

### Primary endpoint

Mean mechanical power. Mechanical power, and mechanical power corrected for endotracheal tube resistance, will be calculated from the continuously recorded inspiratory volume-pressure loop during mechanical ventilation, and compared between groups.

### Participant timeline {13} (Fig. 1)

**Fig. 1 Fig1:**
[figure not shown]
Timeline

The participant timeline is presented in Fig. 1. On the day before surgery, eligible patients will be informed about the study by the study director or his deputy. If the patient agrees to participate in the study, age, height, sex, weight, and American Society of Anesthesiologists physical status will be recorded. On the day of surgery, a peripheral venous cannula will be placed, and standard anesthesia monitoring will be established. An EIT belt will be placed around the chest. After induction of anesthesia according to the local standard clinical protocol, the airway will be managed with a suitable endotracheal tube. After intubation, an arterial access point will be established, and the first blood sample will be collected to analyze lung-specific and inflammatory proteins. Blood gas analyses will be performed hourly, and the inspiratory oxygen fraction will be recorded. EIT measurements will be performed hourly for 5 to 10 min during mechanical ventilation. At the end of surgery, another blood sample will be taken for protein analysis. Patients will be extubated according to standard procedures and transferred to the neurosurgery intensive care unit or to the ward after a stay at the postoperative care unit. A final blood sample will be collected on the first postoperative day for protein analysis.

### Sample size {14}

Unpublished preliminary tests in a physical pulmonary model showed that an increased inspiratory ramp time could reduce mechanical power compared to a short inspiratory ramp time with a partial Eta^2^ of 0.25. Using an ANCOVA with predicted body weight, mean ventilation volume and surgery time, 13 patients per group are needed for gaining a power of 0.8 at a level of significance of 0.05. With an expected dropout rate of 8%, a total of 28 patients are required.

### Recruitment {15}

The patients will be recruited based on named specific inclusion and exclusion criteria. All patients scheduled for elective surgery at the Department of Neurosurgery will be screened by the study personnel. Those who meet the inclusion criteria will be informed about the study and receive informational material by the study director or his deputy. Recruitment is independent of gender, origin, or social status.

## Assignment of interventions: allocation

### Sequence generation {16a}

Participants will be randomly assigned to one of two groups: Ventilation with an increased inspiratory ramp time (study group) or ventilation with a short inspiratory ramp time (control group). Randomization will be done in a 1:1 ratio. The assignment will not depend on any patient factors. A computer-generated block randomization with blocks containing 2 to 6 patients will be used to create a random grouping sequence. The study team will have no access to the randomization list.

### Concealment mechanism {16b}

The allocation will be done using the closed envelopes technique.

### Implementation {16c}

The envelope will be opened by the data collector right before anesthesia starts. The data collector will inform the anesthesiologist about the ventilation settings and will hand out the corresponding ventilation protocol.

## Assignment of interventions: blinding

### Who will be blinded {17a}

During the intervention period, only the patients will be blinded to group allocation. The attending anesthesiologist will necessarily be unblinded during mechanical ventilation but will not be involved in data collection or analysis. Blinding of the data collector will not be feasible in the perioperative period due to his task to ensure adherence to the ventilation protocol. The data collector will take the blood samples and record the ventilation data and the EIT data. The assessor evaluating postoperative pulmonary complications will be blinded to group assignment. All recorded data and all blood samples will be labeled with pseudonyms that do not reveal group assignment, ensuring laboratory personnel and outcome assessors will be blinded. Only during the final overall evaluation can the connection to the group membership be traced back.

### Procedure for unblinding if needed {17b}

Unblinding of the patients upon request is possible after the period of data collection, i.e., after the seventh postoperative day.

Blood samples will be collected after induction of anesthesia, at the end of surgery, and on the first postoperative day to measure the concentration of six lung-specific proteins: soluble receptor for advanced glycation end products (sRAGE), clara cell protein 16 (CCP16), Krebs von den Lungen-6 (KL6), surfactant protein D (SP-D), human type I cell-specific apical membrane protein (HTI56), and growth differentiation factor 15 (GDF-15). The concentrations of the six biomarkers will independently be measured in the laboratory using an Enzyme-Linked Immunosorbent Assay (ELISA). After collection, blood samples will be centrifuged at 2000 × g for 15 min, and the serum will be stored at −80 °C until analysis. For each patient, protein concentrations of all three collection times will be determined and documented. The concentration of the first sample will be used as the baseline. The following concentrations will be compared to this baseline (fold-change). Changes in lung-specific protein levels over time and differences between control and intervention groups will be described.

Additionally, concentrations of two inflammatory biomarkers (PCT and IL-6) will be determined by the Institute of Clinical Chemistry and Laboratory Medicine of the Medical Center. Both the progression of concentrations and the difference between the groups will be analyzed.

Postoperative pulmonary complications will be evaluated for the following 7 days after surgery according to a standardized protocol. For this purpose, the entire patient record and all available results of medical examinations will be screened. Pulmonary complications include the following: Mild to severe respiratory failure, necessity of additional oxygen demand, reintubation or noninvasive ventilation therapy, occurrence of pneumonia, pulmonary edema, pneumothorax, pleural effusion, atelectasis, bronchospasm, or acute respiratory distress syndrome. The rates of these complications will be compared between the two groups.

### Plans to promote participant retention and complete follow-up {18b}

The study period for the primary outcome is completed after surgery. For further secondary endpoints, patient records will be reviewed. A formal participant retention plan is not needed.

### Data management {19}

The data sources include the anesthesia protocol, measured variables (such as ventilation parameters, Horovitz-index and EIT data), and measured protein concentrations. Patient records are also part of the data sources. The data collected in this study are recorded and processed digitally. Patient and disease information is handled confidentially, following data protection laws. These data are stored in a pseudonymized form. Patient data and study data are kept separate from each other. Allocation lists and signed consent forms are stored in different folders on site. Only medical and scientific staff involved in the study can access it.

### Confidentiality {27}

The medical and scientific staff in this clinical study follow medical confidentiality rules and data protection laws to ensure confidentiality of the data. Digital data will be stored securely at the study site and non-digital written data and participant information will be stored in areas with restricted access. All data will be pseudonymized to prevent patient identification, and the pseudonym list, where pseudonym and identity are linked, will be stored separately with access limited to the study director. After complete evaluation of the data, the pseudonym list will be destroyed so that the data become fully anonymized. Any published results will protect the identities of the patients involved.

### Plans for collection, laboratory evaluation and storage of biological specimens for genetic or molecular analysis in this trial/future use {33}

Blood samples will be collected for analysis of lung-specific and inflammatory proteins. Inflammatory proteins will be measured by the colleagues of the Institute of Clinical Chemistry and Laboratory Medicine. Blood samples will be destroyed immediately after testing. Blood samples for analysis of the lung-specific proteins will be stored in the working group laboratory underlying restricted access, until all patient samples have been collected and analyzed by ELISA. After quality and validity check of the results, the remaining blood samples will be destroyed. Any study-related data, including consent forms, will be deleted 10 years after the first publication.

## Statistical methods

### Statistical methods for primary and secondary outcomes {20a}

All results will be analyzed on an as-treated basis. Statistical analysis will be performed using SPSS 29.0.0 software (SPSS Statistics for Windows, IBM, Armonk, NY, USA). Variables will be expressed as mean ± standard deviation or with a 95% confidence interval as appropriate. All statistical tests will be performed with bilateral tests and a *p*-value < 0.05 will be valued as statistically significant.Statistical methods for primary outcomeThe study aims to compare the average mechanical power during the ventilation period between the two groups. This will be done with a two-sided ANCOVA. Predicted body weight, mean minute volume, and surgery time will be used as covariates.Statistical methods for secondary outcomesA linear mixed model with duration of mechanical ventilation and group membership as fixed effects will be used to compare the Horovitz index between the two groups over time. A linear regression with a two-sided 95% confidence interval will be used to estimate the effect of a long versus a short inspiratory ramp time on mean airway pressure and ΔC. The model also includes duration of mechanical ventilation and baseline compliance. Changes in global electrical impedance of the lungs, area, and center of ventilation will be analyzed descriptively. The changes of lung-specific protein concentrations based on sampling times within each group will be analyzed with a linear mixed model. A t-test will be used to compare changes in these protein levels at different time points between the two groups. The change of concentrations of the inflammatory proteins will be described. Postoperative pulmonary complications will be analyzed descriptively.

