
Beyond biological markers and mechanical power, our study will evaluate respiratory system mechanics, Horowitz index, distribution of ventilation, and postoperative pulmonary complications, to cover a broad range of relevant outcomes and potential differences between the two ventilation strategies.

We are aware of several limitations. First, the number of patients is small. However, this first trial focuses on perioperative feasibility and the safety of ventilation modification while conserving resources and minimizing patient risks. If the study results suggest clinically relevant benefits, an extended multicenter investigation will be planned. Second, blinding of the data collector and the attending anesthetist is not possible, which may influence perioperative management or data completeness. Nevertheless, mechanical ventilation will be strictly implemented according to the study protocol. Data recording will be independent, and all analyses will be performed under blinded conditions. Third, besides inspiratory ramp time, the two ventilation strategies differ in the inspiratory-to-expiratory time ratio. Therefore, differences in the mechanical load cannot be attributed solely to the inspiratory ramp time. However, we deliberately chose a reduced inspiratory-to-expiratory time ratio in the study group to facilitate the longest possible inspiratory ramp time to accentuate differences. We are aware that this point must be taken into account in any conclusion. Fourth, the selection of lung-specific proteins is limited. However, additional markers will be analyzed if the planned analysis is inconclusive.

Besides inspiratory ramp time, the two ventilation strategies differ in the inspiratory-to-expiratory time ratio. Therefore, differences in the mechanical load cannot be attributed solely to the inspiratory ramp time. However, we deliberately chose a reduced inspiratory-to-expiratory time ratio in the study group to facilitate the longest possible inspiratory ramp time to accentuate differences. We are aware that this point must be taken into account in any conclusion.

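### Lung-protein analysis: t-tests on fold-changes use the baseline inefficiently, each p < 0.05 counts as significant over 12 comparisons, and the marker list is open-ended

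*Protocol article*

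**What the plan says.** All places are in the protocol article.

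- **Measurements ({18a}).** Blood is taken after induction, at the end of surgery and on the first postoperative day "to measure the concentration of six lung-specific proteins". The first sample is the baseline: "The following concentrations will be compared to this baseline (fold-change". The same section says that group differences will be described.
- **Within-group analysis ({20a}).** "The changes of lung-specific protein concentrations based on sampling times within each group will be analyzed with a linear mixed model".
- **Between-group analysis ({20a}).** "A t-test will be used to compare changes in these protein levels at different time points between the two groups".
- **Significance rule ({20a}).** "All statistical tests will be performed with bilateral tests", and a p-value below "0.05 will be valued as statistically significant". No adjustment is named.
- **Extra markers (Discussion, limitations).** The protein selection is acknowledged to be limited. "However, additional markers will be analyzed if the planned analysis is inconclusive".
- **Additional analyses ({20b}).** None are planned.
- **Samples ({33}).** Protein samples are kept until all have been collected and analysed. "After quality and validity check of the results, the remaining blood samples will be destroyed".
- **Status ({8}).** The trial is an exploratory pilot, and the proteins are secondary outcomes.

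**The concern.** Finding a biomarker of mechanical load is a stated intention of the trial (Background and rationale, Discussion). Three features of the plan weaken what the protein data can say about it.

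1. The between-group comparison rests on a t-test of a ratio to baseline. With about 26 evaluable patients, precision is scarce, and this method gives some of it away. The mixed models describe time courses within each arm and supply no group contrast. Elsewhere {20a} does better: the Horovitz index gets one mixed model with group as a fixed effect, and the compliance change gets a regression that includes baseline compliance.
2. The plan sets a rule that labels each result significant at 0.05 separately, over a dozen comparisons. {18a} says the differences are only described, so their inferential status is unclear.
3. The list of markers can grow in response to the results. That weakens even a hypothesis-generating reading, because the number of looks is then unknown.

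**Working it through.** **The plan's own figure.** No error rate or power is stated for the proteins. The only sample-size figure is for the primary ANCOVA in {14}. With partial eta² = 0.25, f² = 0.25/0.75 = 0.333. A noncentral F with 1 and N − 2 − 3 degrees of freedom and noncentrality f²·N gives power 0.8015 at N = 26 (0.784 at N = 25). So 13 per group reproduces, and 26/0.92 = 28.3 is close to the stated 28. The protein calculations below use 13 per arm.

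**Number of tests.** 6 proteins × 2 follow-up samples = 12. This is derived; the document does not state it.

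**False positives when no protein differs.**
- Independent tests: 1 − 0.95^12 = 0.460, with 12 × 0.05 = 0.6 expected.
- The tests are not independent, since the two follow-up times share a baseline and the markers may be correlated. Simulation (10,000 trials, 13 per arm, assumed log SD 0.5, time correlations 0.5 and 0.7):

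| Assumed marker correlation | log change | fold-change |
|---|---|---|
| 0 | about 43% | about 41% |
| 0.5 | about 36% | about 34% |
| 0.7 | about 29% | about 28% |

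- Range: about 28–46%.
- The error rate of a single t-test on fold-change was 4.5–4.8%.
- Extra markers, two tests each, under independence: one marker, 1 − 0.95^14 = 51%; three, 1 − 0.95^18 = 60%; six, 1 − 0.95^24 = 71%. The number of extra markers is an assumption.

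**Precision.** Let r be the correlation between log baseline and log follow-up, with equal variances. In units of the log variance, a change score has variance 2(1 − r), and the baseline-adjusted residual has variance 1 − r². Their ratio is (1 + r)/2: 0.75 at r = 0.5, 0.85 at 0.7, 0.925 at 0.85.

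Simulated power for one protein at one time (13 per arm, group effect 0.5 SD of log concentration, two-sided 0.05, log SD 0.5 to 0.8):

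| Assumed r | t-test, fold-change | t-test, log change | log ANCOVA |
|---|---|---|---|
| 0.5 | 0.17–0.21 | 0.23 | 0.28 |
| 0.7 | 0.30–0.33 | 0.35–0.36 | 0.38–0.39 |
| 0.85 | 0.57–0.59 | 0.61 | 0.62 |

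Repeat runs agree to about 0.01. Part of the gain comes from taking logs and part from adjusting for baseline.

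**Cost of strict adjustment.** Bonferroni over 12 tests uses 0.05/12 = 0.0042 per test. The family-wise error is then 1 − (1 − 0.0042)^12 = 4.9% under independence. Power for a difference of 1 SD of the analysed quantity at 13 per arm falls from 69% to 30%.

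**The three sections side by side.** The Discussion provides for more markers if the results are inconclusive. {20b} plans no additional analyses. {33} destroys the remaining samples once the results have been checked. Extra assays could be run before destruction, but no section says so, and none says how such results would be labelled.

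**The case against.** The best defence is that this is a declared exploratory pilot with proteins as secondary outcomes. Formal multiplicity control is then a choice, and an expensive one given the drop from 69% to 30%. That stands, and it is why labelling the results is offered below as an alternative to adjustment. It does not cover a rule that calls every p < 0.05 significant, or a marker list that depends on the results.

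Several stronger readings are tempting but not supported:

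- **A false biomarker is likely.** For the 12 planned tests the chance of any false positive stays below one half even under independence. It passes one half only with added markers and near-independent tests. The event counted is also a group difference at p < 0.05; the Discussion would combine protein kinetics with the calculated mechanical energy before naming a marker.
- **Baseline information is wasted.** Fold-change uses the baseline as denominator. The loss is one of efficiency, and it is small at high r.
- **Skewed ratios inflate false positives.** The per-test error rate stayed at or slightly below 5%.
- **The within-group models are misused.** Objective {7} asks about protein kinetics, which these models address, and the plan does not infer a group effect from them.
- **The sections flatly contradict each other.** {33} leaves room for assays before destruction, and the heading of {20b} gives subgroup analyses as its example. This is tension, not an impossibility.

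**Conclusion.** The point holds as a worthwhile improvement to a secondary analysis, not as an invalid analysis. The planned comparison is valid test by test. It gives up power that the same samples could provide: about 0.07–0.11 at r = 0.5, 0.05–0.09 at r = 0.7, and 0.03–0.05 at r = 0.85. The significance rule carries about a 28–46% chance of at least one false positive over 12 derived tests, more if markers are added. The effect size, log SDs, all correlations and the number of extra markers are assumptions; the document gives none of them. The result-dependent marker step is a real fault in the text, and it needs reconciling with {20b} and {33} whatever the correlations are.

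**What to change.** 1. **Model ({20a}).** For each protein, fit one linear mixed model over both groups to log concentration at the end of surgery and on day 1, with group, time, group × time and log baseline. Report the group ratio at each time with a 95% confidence interval. Fold-changes can stay as descriptive figures.
2. **Status of the results.** Either label the protein results hypothesis-generating and make no significance claims, or name one contrast per protein and adjust across six (for example Holm). If both times are to be claimed, adjust across all 12; adjusting across six with two contrasts each would leave the family uncontrolled. Bring {18a} and {20a} into line on whether group differences are described or tested.
3. **Markers.** Fix the list at the six named. Either delete the Discussion sentence on further markers or state that any later marker is post hoc and reported as such. Reconcile this with {20b} and {33}.

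The cost is analysis wording only, with no new patients, samples or assays. {33} keeps the protein samples until collection is complete, so the change can be made before results are seen if the assays have not been run. If adjustment is chosen, the price is the loss of power shown above.
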